### Exploratory analyses

Several exploratory analyses will also be conducted in this study. Specific examples include: (1) The influence of sex on intrusive memory frequency will be examined, as some evidence suggests females experience more frequent intrusive memories following actual [66] and analog [67] trauma exposure during certain phases of the menstrual cycle. (2) In the day-to-day analysis, we will analyze the effect of accumulation of sleep over multiple days on mind wandering and intrusive memory frequency. (3) We will further expand the temporal aspects of the model in Hypothesis 3 to include sleep the night before the lab session (night −1, day 0), to examine sleep’s effect on mind wandering and intrusive memories over a 6-day period. (4) The effect of the nap on mind wandering and intrusive memories on day 0 will also be examined. (5) A further outcome of the mind wandering task will be how many reports of mind wandering are related to the film.

### Subgroup analysis

Exploratory subgroup analyses may include examining only participants who experience intrusions, excluding those who do not experience any intrusive memories following the trauma film. We may also examine intrusion frequency for only those participants who experience a level of distress of four and above (out of 9) when watching the trauma films (completed immediately following the films).

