### Aims and hypotheses

The overall objective of this project is to examine two mechanisms underlying the relationship between sleep and the development of involuntary intrusive memories, utilizing a well-established experimental analog trauma exposure. The two mechanisms are:

Improved memory consolidation over periods of sleep leads to integration of the trauma memory into the broader memory network, thereby reducing intrusive memories.Sufficient sleep quality/quantity facilitates executive control over spontaneous cognition, including intrusive memories, decreasing the likelihood of their occurrence.

This study will employ a between-subjects design, with two conditions: (1) 2-h daytime nap opportunity, measured using polysomnography; and (2) equal length of controlled waking. Each condition will include *n* = 57 healthy adults, aged 18–49 years old (total *N* = 114, aiming for equal numbers of women and men). OSF preregistration: https://doi.org/10.17605/OSF.IO/MWAHD

Aim 1: Examine the effect of a daytime nap (vs. wake) on intrusive memory frequency.
Hypothesis 1.We will replicate the established finding that a nap, relative to wake, will result in a reduced number of intrusive memories [14, 15] in the 5 days following viewing the trauma film.

Aim 2: Investigate the effect of sleep-related memory consolidation on intrusive memory frequency.
Hypothesis 2a.A nap, relative to wake, will lead to greater recognition memory for the trauma film stimuli immediately after the nap/wake period, as measured by improved recognition of trauma stimuli from the film and reduced endorsement of lure stimuli (film images never seen).
 Hypothesis 2b.Recognition memory for the trauma film immediately after the nap/wake period will mediate the relationship between sleep condition (nap vs wake) and the number of intrusive memories in the following 5 days.

Aim 3: Investigate the effect of overnight sleep on mind wandering and intrusive memory frequency over a 5-day period following analog trauma exposure.
Hypothesis 3a.Reduced quantity of sleep at night will be associated with increased mind wandering and greater frequency of intrusive memories the next day.
 Hypothesis 3b.Mind wandering will mediate the relationship between sleep the previous night and intrusive memories the following day.

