**Figure 1 f1:**
[figure not shown]
Timeline of study participation. During days −7 to −1, participants maintain a regular sleep schedule. Day 0 (lab session) is indicative of a participant with a habitual wake time of 8 am. Lab session timing depends on participant sleep schedule. All sessions are a maximum of 6 h long. For the night following the lab session, participants follow the regular sleep schedule. For the remaining four nights of sleep, participants sleep ad libitum. During days 1–5, participants complete a daily mind wandering task (sustained attention task), fill out a diary for intrusive memories, and repeat the recognition task on the final day.

Phase 2 is the lab session (day 0). Participants wake up 2 h prior to their habitual wake time. This is to ensure sufficient sleep during the nap and to mildly sleep-deprive the wake group. After reporting to the lab in the morning participants are set-up with polysomnography. Following this, they view an analog trauma film in a dark sound attenuated room. Participants are then randomly assigned to one of the two groups: an experimental (nap) group and a controlled (wake) group, for a 2-h period. During this time, those in the wake group can engage in specific activities provided by the researchers including coloring and puzzles. They are unable to use social media, watch videos, view photos, read, or engage in university study/other work during this time. At the end of this experimental period, polysomnography equipment is removed and there is a 30-min delay period for both groups, to allow for the effects of sleep inertia to subside for the nap group. Participants then complete a recognition memory task for images from the trauma film and a sustained attention task to measure mind wandering (hereinafter referred to as “mind wandering task”) in the same sound attenuated room. Following this, participants are provided with instructions for completing an intrusive memory diary.

Phase 3 includes the remaining 5 days of the experiment. Over the next five nights, we will continue to monitor participant sleep with diaries and actigraphy. Participants complete daily intrusive memory diaries, starting as soon as they leave the lab, with six entries at minimum. During each day, they complete the same mind-wandering task completed during the lab session. The recognition task is repeated on day 5. Following study completion, participants attend a debrief meeting.

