### Participants and recruitment

#### Sample size

Our target sample size is 114 participants, with 57 in each condition. This study is powered primarily on Hypothesis 1, the group effect (nap vs. wake) on intrusive memory frequency. Relevant effect sizes were derived from a variety of prior studies, which have also been reported within at least one of four meta-analyses. Previous studies [14, 15, 25] examining the effect of a nap compared to wake on intrusion frequency have detected small to medium effect sizes (Hedges’ *g* = 0.38 [26] and 0.69 [15]) for between-group differences in intrusive memory frequency in the days following the experimental manipulation. Gvozdanovic et al. (2023) [14] also found a nap led to significantly fewer intrusive memories than the wake group, however, an effect size was not provided. For studies examining recognition memory for the trauma film following overnight sleep compared to wake or partial sleep deprivation [13, 23, 40], we calculated a sample size weighted average for Cohen’s *d*, finding a medium effect size of 0.5 for between-group differences where sleep, relative to wake, led to improved recognition memory for the film. Consistent with these studies, to detect a medium effect size of 0.5, with a two-tailed α of 0.05 and 80 per cent power, 57 participants are needed per group (114 participants in total) [41].

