##### Trauma film paradigm

The trauma film paradigm is used in this study to elicit intrusive memories [17]. Clips from two films are viewed in a small, sound attenuated room, and presented on a 24-inch screen with over-ear headphones for audio. Participants first complete a questionnaire about their current emotional state. They watch the trauma film (~12 min in total), which includes two scenes, one from the film Irréversible [57] and the other from a UK public safety advertisement on the dangers of texting and driving [58]. Both film scenes are fictional and have been used in previous studies [56, 59–63]. Film order is counter-balanced. Whilst participants view the films, we ask they maintain their concentration and continuously look at the scene. Upon completion, they rate their current level of distress and degree to which they were able to pay attention to the films. A camera in the room is used to monitor participants’ attention to the film. Participants are told prior to participating in the study they may watch positive, neutral or negative scenes, and are informed about the contents of the negative scenes prior to watching.

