##### Intrusive memory diary (days 0–5)

Following completion of the cognitive tasks, participants are provided with a definition of intrusive memories and instructions for completing the intrusive memory diary. The diary is completed online, accessible via smartphone, or computer. There are a total of seven questions, including the date and time of the intrusion, the type (eg, image, sound, thought(s)), content of the intrusive memory, whether the intrusive memory was triggered, and level of distress and vividness rating. This diary was based on an online diary used in a trauma film study by Zeng et al. (2021) [13].

An email with the intrusive memory diary link is sent to participants as soon as they leave the lab on day 0. Participants are instructed to complete the diary as soon as possible following the experience of an intrusive memory, completing this as many times as needed. A reminder with the intrusive memory diary link is also sent via text message to participants each evening (between 1 and 3 h prior to scheduled bedtime, based on the previous week), beginning the first evening following the lab session. Participants are instructed to fill out the diary at the end of the evening after receiving the text reminder, even if they have not experienced an intrusive memory. Participants can select an N/A option to each of the diary questions, reducing demand characteristics to report an intrusive memory even if one did not occur. Thus, participants complete the diary a minimum of six times. The primary outcomes from the intrusive memory diary are the total number of intrusive memories following the lab session and number of intrusive memories each day. Secondary outcomes include examining level of distress ratings (1 = not at all distressed, 9 = extremely distressed) when intrusive memories occur.

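### The optional subgroup of participants with intrusions selects on the Hypothesis 1 outcome after randomisation, so any nap-versus-wake comparison within it should be labelled descriptive

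*Protocol article*

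**What the plan says.** The Subgroup analysis section of the protocol article offers two optional subgroups. The first is defined by the diary: "Exploratory subgroup analyses may include examining only participants who experience intrusions, excluding those who do not experience any intrusive memories following the trauma film". The second keeps participants whose distress while watching the films reached 4 or more out of 9.

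Four other places fix what the first subgroup means:

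- **Outcome.** Under Intrusive memory diary: "The primary outcomes from the intrusive memory diary are the total number of intrusive memories following the lab session", together with the number on each day.
- **Expected effect.** Hypothesis 1, under Aims and hypotheses, is that "a nap, relative to wake, will result in a reduced number of intrusive memories".
- **Order of events.** Under Study design (text after the Figure 1 caption), the film comes first. Then "Participants are then randomly assigned to one of the two groups". Only after the nap or wake period and the tasks does the diary begin: "Participants complete daily intrusive memory diaries, starting as soon as they leave the lab".
- **Distress.** The diary section adds "Secondary outcomes include examining level of distress ratings", given on a 1 to 9 scale and only for intrusions that occur.

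The rating behind the second subgroup is made straight after the film: "Upon completion, they rate their current level of distress and degree to which they were able to pay attention to the films". That precedes the nap or wake period.

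**The concern.** Membership of the first subgroup is the Hypothesis 1 outcome dichotomised at zero. The randomised condition is expected to change that outcome. If the nap works, more people in the nap arm end with no intrusions and drop out of the subgroup, and the two remaining groups are no longer the groups that were randomised. The film-distress subgroup does not have this problem, because its rating precedes the manipulation. The section lists the two side by side with no caution about the difference.

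What is at stake is interpretation. The subgroup leaves out anyone in whom the nap prevented intrusions altogether. A weak or null result among the rest could be taken as evidence about the nap's effect on people who do have intrusions, and it would not support that reading. Zeros are a practical possibility here: the Aim 3 text under Analytic strategies allows for too many zero counts to run the mediation models.

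**Working it through.** The plan gives no figure for this point: no expected mean count, dispersion or share of zeros. The counts below are assumptions. The only figure taken from the plan is the arm size of 57 (Sample size section), and nothing here depends on how it was derived.

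**Formula.** Let μ be an arm's mean count and P0 its share with no intrusions. The mean among those with at least one is μ / (1 − P0). Hence:

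subgroup ratio = true ratio × (1 − P0 wake) / (1 − P0 nap).

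If the nap raises the share of zeros, the last factor exceeds 1 and the ratio rises. For a negative binomial with dispersion k, P0 = (1 + μ/k)^(−k). With k = 1 this is 1/(1 + μ), and the conditional mean is 1 + μ.

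**Common multiplicative effect, k = 1, true ratio 0.60.**

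| Wake mean | Nap mean | P0 wake | P0 nap | Mean if any, wake | Mean if any, nap | Subgroup ratio | Left of 57, wake / nap |
|---|---|---|---|---|---|---|---|
| 3 | 1.8 | 0.250 | 0.357 | 4.0 | 2.8 | 0.70 | 43 / 37 |
| 1.5 | 0.9 | 0.400 | 0.526 | 2.5 | 1.9 | 0.76 | 34 / 27 |

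**Rare zeros.** Poisson counts, wake mean 8, true ratio 0.50: P0 is e^(−8) = 0.0003 (wake) and e^(−4) = 0.018 (nap). The subgroup ratio is 0.50 × 0.9997 / 0.982 = 0.51.

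**Common zeros.** Poisson counts, wake mean 1, true ratio 0.50: P0 is 0.368 and 0.607. The subgroup ratio is 0.50 × 0.632 / 0.393 = 0.80.

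**Vanishing (wake mean 3, k = 1).** Suppose the nap clears all intrusions in a random 40% of participants and changes nothing in the rest. The nap mean is 0.6 × 3 = 1.8, a true ratio of 0.60. The nap share with none is 0.25 + 0.40 × 0.75 = 0.55. The mean if any is 1.8 / 0.45 = 4.0 in the nap arm and 4.0 in the wake arm, so the subgroup ratio is 1.00.

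**Reversal (same wake arm).** P(1) = 0.1875 and P(2) = 0.1406. Suppose the nap clears all intrusions in 60% of people who would have had one or two.

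- Mean removed: 0.6 × (0.1875 + 2 × 0.1406) = 0.281. Nap mean 2.719, true ratio 0.91.
- Nap share with none: 0.25 + 0.6 × 0.3281 = 0.447.
- Mean if any: 2.719 / 0.553 = 4.92, against 4.0 in the wake arm. Subgroup ratio 1.23.

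The 60% matters. Clearing all such people gives a true ratio of 0.84 and a subgroup ratio of 1.50.

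**Precision.** In simulated t-tests with 57 per arm (negative binomial, k = 1, wake mean 3, true ratio 0.50), power was 84% with everyone and 64% in the subgroup, where about 43 wake and 34 nap participants remained.

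**The case against.** The strongest reply is that the text commits to very little. The analysis is exploratory and optional, and the section does not say that the subgroup will be compared by condition. It could serve to describe intrusion content, or within-person links between sleep and intrusions. This stands in part. The next sentence, on the film-distress subgroup, uses a word implying that intrusion frequency is the outcome for the first subgroup too, but the contrast between conditions is not spelled out. The criticism therefore applies to any such comparison and does not allege that one is promised. The exploratory label limits how much weight a result carries; it does not remove the selection. Nor does the possibility of a fuller analysis plan, because the article itself states the exclusion.

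A reader might infer that Hypothesis 1 is biased. The documents do not support that. The Data exclusion section does not list having no intrusions among its reasons for exclusion, and the diary lets participants record that none occurred.

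A reader might also infer that the subgroup would be expected to hide or reverse a real nap effect. That goes too far. Under a common multiplicative effect the ratio only shrinks towards 1. The vanishing and reversal cases need particular mechanisms, and the documents give no evidence for or against them.

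Two further objections stand. The count part of a hurdle model uses the same selected people, so it does not restore randomisation and must be labelled accordingly. And distress is openly defined as conditional on an intrusion, with no hypothesis or stated model comparing it by condition, so replacing it with a summed score would be a preference and not a correction.

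**Conclusion.** The point holds in limited form. The proposed subgroup is selected on the Hypothesis 1 outcome after randomisation, so a nap-versus-wake comparison inside it is not randomised. With a common multiplicative effect, dispersion 1 and a true ratio of 0.60, the ratio seen would be 0.70 (wake mean 3) or 0.76 (wake mean 1.5). The shift is close to nothing when zeros are rare and large when they are common. Disappearance or reversal is possible only if the nap acts mainly on whether any intrusion occurs or on people with few intrusions.

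All sizes rest on assumed counts, because the documents give no mean, dispersion or share of zeros. They refer to the ratio of means: under strong overdispersion the standardised difference may barely change or even rise slightly. Severity is minor, since only an exploratory analysis is touched.

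**What to change.** In the Subgroup analysis section, replace any comparison by condition among participants with intrusions with a two-part (hurdle) analysis of all randomised participants with diary data:

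1. Any intrusion (yes or no) by condition, in a logistic model.
2. The count among those with at least one, by condition, in a zero-truncated negative binomial model.

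Report both parts beside the overall rate ratio from the Aim 1 analysis. State that the second part is descriptive and is not a randomised effect of the nap. If distress ratings are compared by condition, attach the same statement; a summed distress score is not required. The film-distress subgroup can stay as it is on this count.

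The change is to analysis text only and needs no new data. The article says that final analysis starts after data collection, estimated to run to July 2026. The downside is that readers must be given two estimates and told how they differ.

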### Data management plan

All sleep recordings including polysomnography and actigraphy recordings are stored on a Monash University server. Self-report data, including sleep diaries and intrusive memory diaries, are collected using Qualtrics. Links are sent to participants via text reminder. Questionnaires assessing trait-level spontaneous cognition are collected via Qualtrics or pen-and-paper during PSG set-up on the day of the lab session. The recognition memory task is also completed using Qualtrics. The mind wandering task is completed using Inquisit (Millisecond Software). Participants are provided with a participant code prior to completing any measures, including screening questionnaires. Participant codes are associated with questionnaires, diaries/tasks, and polysomnography data. Only researchers associated with the study have access to Qualtrics and the Monash University server.

### Data sharing and dissemination

Final data analysis will begin after completion of data collection. Partial study results may be presented at national and international conferences. Full study results will be disseminated via peer-reviewed publication and conference presentations. Following publication, a summary of results will be sent to participants who completed the study, in recognition of their participation. Following publication of primary outcomes, de-identified participant data and code will be made available in an accessible data repository.

## Discussion

A growing body of research demonstrates sleep reduces the frequency of intrusive memories following experimental trauma exposure [13–16, 23, 24]. Studies examining trauma-exposed populations and persons with PTSD also suggest sleep may affect the frequency of intrusive memories both in the early aftermath [10, 11] and years after trauma exposure [12]. The current study builds on previous research examining the effect of sleep on intrusive memories following experimental trauma exposure, to examine *how* sleep exerts this effect on intrusive memory frequency. To do this, we are experimentally manipulating sleep immediately following viewing a trauma film and monitoring sleep over the following five nights. Participants also record intrusive memories, report mind wandering frequency during a sustained attention task and complete a recognition task for trauma film stimuli to examine whether memory consolidation and executive control over spontaneous cognition mediate the relationship between sleep and intrusive memories.

While the trauma film paradigm is a well-established method to elicit and study intrusive memories, there are several limitations to be considered. The trauma film is not real trauma exposure and distress in response to the film is unlikely to be as high as in real world trauma. Despite this, the paradigm consistently produces a sufficient analog trauma response to be modulated by sleep, although distress associated with intrusive memories in this paradigm is not reliably elicited [13, 14, 26, 40, 68]. Other external validity issues include the peripheral experiences related to the primary trauma incident, which may further increase distress (eg, attending an emergency department or providing a statement to police), which this paradigm is unable to simulate. As participants are informed that they may watch a disturbing film, there may also be a risk of selection bias. Those choosing not to participate may be more concerned about potential film content, and possibly more likely to experience the intrusive memories we are attempting to measure.

During development of the recognition task, pilot participants rated images for valence, distress, and clarity, to ensure these domains were similar across targets and lures (see Supplementary Material S1). As this was a separate cohort of participants who were not exposed to the trauma films, there is still likely to be inter-individual variability across valence and distress associated with the images, which could affect recognition. However, we did not include distress ratings of each image during the recognition task, to reduce participant burden. Finally, all tasks (mind wandering and recognition) in the final 5 days of the study are completed at home. While participants are instructed to complete the tasks in quiet environments and task timing and performance is monitored by researchers; these are completed in less controlled environments relative to the lab session on day 0. At the same time, task completion from home reduces participant burden in this study, enabling the investigation of a potentially important mechanism (executive control over spontaneous cognition) that may have otherwise been difficult to examine over a 5-day period in laboratory conditions.

Despite these limitations associated with the use of trauma films, this paradigm does reliably induce intrusive memories of the films and has been extensively used to examine factors influencing intrusive memory frequency [17]. As prior research has examined sleep and intrusive memories in both healthy and trauma-exposed populations, a strength of the present study lies in its aim to replicate previous findings and extend this line of research in several ways. Firstly, we are extending upon three studies which have examined explicit trauma memory following a period of overnight sleep [13, 23, 40] by examining this following a nap. If naps enhance explicit trauma memory in addition to reducing intrusive memories, this will provide further support for the memory consolidation account [36]. Secondly, to investigate an executive control hypothesis, we are examining day-to-day relationships between sleep and intrusive memories, similar to research examining multiple periods of sleep in the immediate aftermath [10, 11] and many years following actual trauma exposure [12]. Finally, we are investigating the effect of sleep architecture and micro architecture on intrusive memory frequency, following studies linking REM to reduced intrusion-related distress [26] and sleep micro-architectural features (N2 sleep spindles, REM theta) to fewer intrusions [16, 24]. Moreover, persons with PTSD exhibit REM abnormalities in addition to sleep disturbance [69, 70]. Overall, findings from this study will provide insights into how sleep affects the development and possible maintenance of a key re-experiencing symptom of PTSD and provide further direction for mechanistic research, including examining these mechanisms in trauma exposed populations and/or those experiencing sleep disorders.
